##### PE analysis without baseline covariates

A PE analysis on the first-time and the overall infections will be also performed by removing all the baseline covariates from the cloglog models and only keeping “intervention group” as the only covariate (in addition to visit, as a categorical predictor per the model assumptions and set-up). The hazard ratios between SR and placebo will be provided, along with 2-sided 90% CIs.

##### Effects of SR on entomological endpoints

The endpoints in the entomological analysis will include the HBR (number of anopheline caught during the 12-hr interval overnight), anopheline parity rate, anopheline sporozoite rate, anopheline EIR, and the anopheline indoor density collected by light-trap.

We will report the frequencies and proportions of each mosquito Genus and species (anopheline and non-anophelines) collected using HLC and light trap methods across clusters and treatment arm.

The time profile plots of each aggregated entomological endpoint will be obtained over the baseline and intervention period. An appropriate statistical model for the HBR will be identified after examining the distributional characteristics of the HBR data, which are likely to follow (zero-inflated) Poisson distribution, or (zero-inflated) negative binomial distribution if there is over-dispersion. The covariates in the models will include the fixed effects of intervention, time, cluster population size, number of houses in a cluster, location (inside or outside), location and intervention interaction; and a random effect for cluster. The ratio between SR and placebo in HBR will be estimated. A similar model will be applied to analyze the density of mosquitoes caught by light traps. The ratio between SR and placebo on light trap density will be estimated.

The model for parity rate will be the (zero-inflated) Poisson distribution or a (zero-inflated) negative binomial distribution with the daily porous mosquitos as the outcome and the daily HBR as the offset, and the same set of covariates as those used in the model for analyzing HBR. The model for the sporozoite rate will be similar to the parity rate with the change of outcome variable to daily mosquitos with positive sporozoite. Note, if the data on parity and sporozoite positivity are highly unbalanced (not in terms of the distributions between the treatment arms, but the marginal distribution of the variable itself; e.g., 99% nulliparous or 99% negative sporozoite), then the model might lead to unstable estimates or the model might not even converge. In such cases, only summary statistics will be provided.

Summary statistics will be provided on EIR and the insecticide resistance at baseline and per year during the intervention period by treatment group.

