## Assignment of interventions: allocation

### Sequence generation {16a}

The unit of randomization for the intervention and placebo will be a cluster. For the baseline cohort, the recruitment of participants for enrollment was based on the random selection of HHs using census mapping of the study area. The study statistician will analyze data from the baseline follow-up period to inform on potential stratification requirements prior to randomization. Criteria for stratification will be baseline malaria incidence levels and/or adult entomological endpoints. Following stratification (as needed), clusters will be allocated to receive either active or placebo treatment using a random number generator (https://www.random.org). Following cluster treatment allocation, a simple random sample will be completed for the selection of sub-clusters assigned for entomology collection. The cluster allocation code will be made available from the intervention manufacturer to the Data Safety Monitoring Board (DSMB) for use in safety assessments. The site database manager will assign a unique identification number to each household (HIN) and the site intervention administrator will coordinate the distribution of blinded active or placebo to enrolled HHs within each cluster corresponding to the pre-labeled package code.

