#### Entomological collections

Twenty clusters (10 SR, 10 placebo) will be randomly selected to estimate the impact of the SR on entomological measures of malaria transmission. Within each cluster, light trap collections will be conducted monthly in 10 randomly selected HHs to assess the impact of SRs on the density of *Anopheles* mosquitoes indoors. The light traps will be deployed next to a person sleeping under a net and will run from approximately 6 pm to 6 am. The 10 SR and 10 placebo clusters will be randomly selected at the beginning of the study and will remain fixed throughout the study. HHs will be sampled with replacement and therefore will be eligible for repeated sampling throughout the study. HHs enrolled in the cohort study will not be eligible for mosquito sampling.

HLCs will be done indoors and outdoors in 6 intervention and 6 control clusters (the 12 clusters will remain fixed throughout the study) in four houses (randomly selected) in each cluster for the period of 2 nights (total of 48 houses across both arms) once every quarter (3 months) to determine the effect of SR on the host-seeking behavior of mosquitoes. The same clusters and the houses will be sampled each sampling period. SR and placebo clusters will be selected in pairs to reduce the degree of heterogeneity between two arms. Sentinel houses will be chosen so they are balanced as to house design and inhabitants to reduce bias due to mosquito density heterogeneity (i.e., some houses may be more attractive to mosquitoes than others). HHs with children enrolled in the cohort are not eligible for the HLCs. One pair of clusters will be sampled on any given night. Collections will start at 6 pm each night with one person inside and one person outside. The teams will collect for 45 min each hour and then take a 15-min break before starting the next hour of collection. At midnight, a new team will begin collecting and will continue until 6 am. Mosquitoes will be sorted by site, date, and time of collection. All mosquitoes will be identified to species and all female anopheline mosquitoes will be tested for the presence of sporozoites by ELISA and/or PCR. A subset of up to 30 per cluster per sampling period will be dissected for parity.

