### Interim analyses {21b}

No interim analysis will be performed on the malaria and entomological data collected from the intervention period post randomization. The baseline data will be analyzed at the mid-point of the baseline period and at the completion of the baseline period to estimate the first-time and overall infection rates and their variability, and the mosquito density across the enrolled clustered.

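### The entomology models list their covariates but leave out each cluster's baseline mosquito density, which is collected; the timing of the entomology cluster draw is also contradictory

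*Protocol article*

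**What the plan says.** All references are to the protocol article.

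- **Covariates.** Under Effects of SR on entomological endpoints, the HBR model is specified thus: "The covariates in the models will include the fixed effects of intervention, time, cluster population size, number of houses in a cluster", followed by "location (inside or outside), location and intervention interaction; and a random effect for cluster". The parity and sporozoite models take over the same covariates. For light traps, "A similar model will be applied to analyze the density of mosquitoes caught by light traps".
- **Baseline data.** Interim analyses {21b} has the baseline data analysed for infection rates "and the mosquito density across the enrolled clustered". The entomology section plots each endpoint over baseline as well as intervention. Sequence generation {16a} names adult entomological endpoints as a possible stratification criterion.
- **Cluster numbers.** For HLC: "HLCs will be done indoors and outdoors in 6 intervention and 6 control clusters". For the wider entomology sample: "Twenty clusters (10 SR, 10 placebo) will be randomly selected to estimate the impact of the SR on entomological measures of malaria transmission".
- **Pairing.** Entomological collections says that HLC clusters are chosen as SR/placebo pairs to limit heterogeneity, and "One pair of clusters will be sampled on any given night".
- **Timing of the draw.** Sequence generation {16a}: "Following cluster treatment allocation, a simple random sample will be completed for the selection of sub-clusters assigned for entomology collection". Entomological collections instead selects the 10 and 10 clusters at the beginning of the study, and Trial design {8} fixes the HLC houses when baseline starts.

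**The concern.** Baseline density of the same mosquitoes, caught by the same method in the same clusters, is the obvious candidate to explain differences between clusters at follow-up. The protocol considers it useful enough to stratify on. The analogous measure on the malaria side, baseline incidence, is listed as a cluster-level covariate in the section relating epidemiological and entomological endpoints. The entomology models use cluster population size and number of houses instead.

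With so few clusters, chance differences in density between the arms go straight into the SR/placebo ratio. The random cluster effect lets the standard error reflect that variation but does not reduce it. The outcome definitions confine HBR and light-trap density to the 24-month intervention period, so baseline counts do not enter as outcomes either.

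At stake is the precision of secondary endpoints meant to supply entomological correlates and benchmarks for later products. The contradiction on timing matters here because clusters first drawn after allocation might have no baseline density to adjust for.

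**Working it through.** **1. The plan's own figure.** The only power figure is for malaria: 788 events, with one-sided 5% error, PE 30%, CV 0.47, 30 clusters per arm and a rate of 1.0 per person-year. The Hayes-Bennett rate formula without the extra cluster is c = (zα + zβ)² [(λ0 + λ1)/y + k²(λ0² + λ1²)] / (λ0 − λ1)².

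- 30 × 0.09 / 6.183 = 0.4367, and 0.47² × 1.49 = 0.3291.
- So 1.7/y = 0.1076, and y is about 15.8 person-years per cluster.
- Events = 30 × 1.7 × 15.8, about 806, which is 2.3% above 788.

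The malaria figure therefore reproduces closely. No power figure is given for entomology.

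**2. Entomology set-up.** Inputs from the protocol are m = 6 per arm (HLC), m = 10 per arm (light traps) and the covariate list. Assumptions are:

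- a mosquito CV of 0.47, borrowed from the malaria hazard, with 1.0 as a sensitivity value;
- count error within clusters ignored;
- a cluster-level comparison of log densities with a t reference;
- ρ, the baseline/follow-up correlation of log density beyond what the listed covariates explain.

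Formulas:
- SD of log density = √ln(1 + CV²) = √ln(1.2209) = 0.447.
- SE of the log ratio = 0.447 × √(2/m), which is 0.258 for HLC.
- Degrees of freedom under the listed covariates = 2m − 2 − 2, which is 8 for HLC and 16 for light traps.
- Adding baseline density multiplies the variance by (1 − ρ²) and costs 1 df.

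**3. Results at CV 0.47.** Half-width is that of the 90% two-sided interval on the log ratio. Detectable is the reduction found with 80% power at one-sided 5%.

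| Model | HLC half-width | HLC detectable | Light-trap half-width | Light-trap detectable |
|---|---|---|---|---|
| Listed covariates | 0.480 | 50% | 0.349 | 41% |
| + baseline, ρ = 0 | 0.489 | 51% | 0.350 | 41% |
| + baseline, ρ = 0.3 | 0.466 | 49% | 0.334 | 39% |
| + baseline, ρ = 0.5 | 0.423 | 46% | 0.303 | 36% |
| + baseline, ρ = 0.7 | 0.349 | 40% | 0.250 | 31% |

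For HLC the interval is 12% narrower at ρ = 0.5 (0.423/0.480) and 27% narrower at ρ = 0.7 (0.349/0.480). At CV 1.0 and ρ = 0.7, the detectable reduction goes from 73% to 61% for HLC and from 62% to 50% for light traps.

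**4. Break-even.** Adjustment pays when √(1 − ρ²) × t(df − 1) < t(df). For HLC, 1 − ρ² = (1.860/1.895)² = 0.963, so ρ is about 0.19. For light traps, with 16 and 15 df, it is about 0.09.

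**5. Pairs.** Fixed pair effects added to the HLC list leave m − 1 − 2 = 3 df and multiply the variance by (1 − ICC). At ICC 0 the half-width is 0.607, against 0.480 without them. At ICC 0.7 it is 0.332. Break-even is an ICC of about 0.38.

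**6. Timing, side by side.** Sequence generation draws the entomology clusters by simple random sampling once arms are assigned. Entomological collections has them chosen at the outset, with HLC clusters in pairs. Trial design has the HLC houses, and hence their clusters, fixed when baseline starts. The study timeline puts allocation in January 2022, after baseline. These cannot all be followed: they differ both on when and on how the clusters are chosen.

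**The case against.** The strongest reply is that this is an article, that wording such as will include does not close the list, and that a separate SAP could add terms. Randomisation keeps the SR/placebo ratio valid without adjustment, so leaving out a precision covariate is not an error. The possible stratification and the paired, balanced HLC sampling already give some protection. This limits the severity. It does not remove the point, because the protocol names specific covariates and passes over one that its own design supplies.

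The size of the gain is also open to challenge, fairly. The correlation is assumed. A six-month baseline with quarterly HLC holds about two rounds, of two nights in four houses per cluster, so the HLC baseline is noisy and the correlation may be modest. At 0.3 almost nothing changes, and below about 0.19 adjustment loses slightly.

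A reader might infer several stronger things that the documents do not support:

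- **That drawing clusters after allocation itself wastes precision.** It does not, and it is one side of a contradiction rather than the settled plan.
- **That adjustment is worth 1.33 to 1.96 times as many clusters.** Those figures are 1/(1 − ρ²) at 0.5 and 0.7. They ignore count error within clusters and anything the existing covariates already explain.
- **That a pair or night term is a free gain.** Each night contains one SR and one placebo cluster, so night effects largely cancel in the contrast. Omitting the term mainly makes the standard error conservative, and time, on an unstated scale, may absorb part of it. Fixed pair effects could lose precision.
- **That population size and number of houses are redundant.** Nothing in the article shows this. Dropping one of them is a preference.
- **That all entomology rests on 6 against 6.** That applies to HLC only; light traps have 10 against 10.

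**Conclusion.** The point holds in a limited form. The stated covariate list omits baseline density, which is collected, and adding it is a cheap improvement that probably helps. Under the assumptions above, the HLC detectable reduction improves by roughly 1 to 10 percentage points for correlations from 0.3 to 0.7, and the light-trap figure by up to about 10 points at 0.7. The light-trap case is the safer one, since its break-even correlation is only about 0.09. The pairing gain is conditional. The contradiction over when and how entomology clusters are chosen is real and needs resolving in its own right. These are secondary endpoints: neither the validity of the randomised comparison nor the primary malaria conclusion is affected.

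**What to change.** 1. In the HBR and light-trap models, add the cluster's log baseline mean density from the same collection method, with a small pre-stated constant for zeros, and any stratification factor used in the allocation. State whether the parity and sporozoite models inherit these terms. The cost is about one cluster-level degree of freedom for baseline density, plus any spent on stratification terms. It is a wording change that can be made while the biostatistician is still blinded.
2. Optionally, for HLC, add a random (not fixed) pair or pair-night effect to reflect the paired sampling.
3. Reconcile Sequence generation {16a} with Entomological collections and Trial design {8}. State when the 20 and 12 clusters were chosen, whether by simple random sampling or in pairs, and how the 10:10 and 6:6 splits were obtained. The clusters analysed should be those with baseline data. If clusters were in fact drawn after allocation and lack such data, say so, because item 1 then cannot be applied to them.

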### Trial design {8}

The study design is a cluster randomized control double-blinded clinical trial with 30 clusters per treatment arm (SR intervention and placebo), with a 6-month baseline follow-up period, and a post cluster randomization follow-up period of 24 months with intervention. For the evaluation of the primary objective, 26 subjects (HHs) are required within each cluster factoring in a 35% loss-to-follow-up (LTFU) rate. It is expected that 80% of the baseline subjects (HHs) will continue to participate in the intervention period therefore a total of 32 subjects (HHs) will be enrolled at the start of baseline. At least one child aged from ≥ 6 months to < 10 years of age from each HH will be recruited for malaria follow-up during each baseline and intervention trial periods.

Twenty clusters (10 SR, 10 placebo) will be randomly selected to estimate the impact of the SR intervention on entomological measures of malaria transmission using CDC light traps. From these 20 clusters, a subset of 12 clusters (6 SR, 6 placebo) will be randomly selected for HLC. Light trap collections will be conducted in 10 randomly selected houses every month to assess the impact of the SR intervention on the indoor density of *Anopheles* mosquitoes. Indoor HLC will be conducted in four randomly selected houses within each of the subset 12 clusters every quarter. Four houses will be randomly selected at the start baseline, for a total of 48 sentinel houses). These 48 houses will remain fixed throughout the trial period.

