### Outcomes {12}

The primary outcome measure of this cRCT will be the number of first-time malaria infections (*Plasmodium falciparum* (Pf)) during the intervention period (24 months) as measured by microscopy in children aged between 6 months and 10 years.

Secondary outcome measures include:
2.Number of overall new *Plasmodium falciparum* malaria infections during the intervention period (24 months) as measured by microscopy in children aged between 6 months and 10 years;3.Number of first-time *Plasmodium falciparum* malaria infections during the intervention period (24 months) by two age groups (≤ 6–59 months old; 5–10 years old) as measured by microscopy in children aged between 6 months and 10 years;4.Number of overall *Plasmodium falciparum* malaria infections during the intervention period (24 months) by two age groups (≤ 6–59 months old; 5 years to 10 years old) as measured by microscopy in children aged between 6 months and 10 years;5.Anopheline-human contact (indoor and outdoor) using human biting rate (HBR) as an indicator for all anophelines and by anopheline species as measured by human landing catch (HLC) during 12-h intervals on a quarterly basis during the intervention period (24 months);6.Anopheline parity rate as an indicator of population age structure for all anophelines and by anopheline species as measured by mosquito ovarian dissections from a sub-sample of anophelines collected during HLC procedures during the intervention period (24 months);7.Anopheline infectivity using sporozoite rate as an indicator for all anophelines and by anopheline species as measured by laboratory detection of sporozoites in mosquito head-preps from a sub-sample of anophelines collected during HLC and/or CDC-light trap procedures during intervention period (24 months);8.Anopheline infectivity using entomological inoculation rate (EIR) during the intervention period (24 months) as an indicator for all anophelines and by anopheline species as measured by calculating the number of sporozoite-infected anopheline mosquitoes captured per person during intervention period from HLC and/or CDC-light trap procedures;9.CDC-light trap indoor density for all anophelines and by anopheline species as measured by CDC-light trap collections during 12-h intervals on a monthly basis during the intervention period (24 months);10.Insecticide resistance as measured by WHO filter paper test and CDC bottle assays during the baseline (6 months) and intervention period (24 months);11.Adverse events (AEs) and serious adverse events (SAEs) as measured by solicited and unsolicited reports during baseline (6 months) and intervention period (24 months). Mean, minimum and maximum frequency, and percentage of AEs and SAEs across clusters among enrolled subjects will be summarized by the treatment arm.

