#### Statistical methods—secondary endpoints

##### PE of SR against the overall (both first-time and recurrent) malaria infection

The secondary hypothesis on PE against the overall new malaria infections will be tested by comparing the hazard rates of the overall malaria infection between SR and placebo in the ITT population. using a similar approach as for the first-time infection with an additional random effect term to account for the dependency among the multiple malaria incidences collected from the same individual. PE against the overall infections is estimated by ($$ 1-\mathit{\exp}\ \left(\hat{\beta}\right)\ \Big)\times $$100%, where$$ \hat{\beta} $$ is the estimated regression coefficient associated with the treatment group, with a 90% 2-sided CI based on the Wald test. The lower bound of the 90% CI corresponds to the lower bound of the 95% 1-sided CI (the hypothesis is one-sided).

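### The landing-catch model gives the location-by-intervention term no error component at its own level, so the interval for the indoor-versus-outdoor difference in repellent effect will be too narrow if the indoor:outdoor ratio varies between houses or clusters

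*Protocol article*

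**What the plan says.** Under *Entomological collections*, "HLCs will be done indoors and outdoors in 6 intervention and 6 control clusters", "in four houses (randomly selected) in each cluster for the period of 2 nights (total of 48 houses across both arms) once every quarter". On each collection night, "Collections will start at 6 pm each night with one person inside and one person outside". The sites do not change: "The same clusters and the houses will be sampled each sampling period". *Trial design {8}* says the same of the sentinel houses: "These 48 houses will remain fixed throughout the trial period". *Outcomes {12}* lists anopheline-human contact, indoor and outdoor, as a secondary outcome measured "on a quarterly basis during the intervention period (24 months").

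For analysis, *Effects of SR on entomological endpoints* names a Poisson or negative binomial model, zero-inflated if needed. Its fixed effects are intervention, time, cluster population size and number of houses, followed by "location (inside or outside), location and intervention interaction; and a random effect for cluster". The SR/placebo ratio in HBR is to be estimated. The same covariates are reused for the parity and sporozoite models. No house term and no location-specific random effect is named.

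For recurrent infections in the same child, by contrast, the malaria analysis has an "additional random effect term to account for the dependency among the multiple malaria incidences collected from the same individual".

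**The concern.** The indoor and outdoor catches are paired within house and within cluster, and the pairs recur for two years. The interaction asks whether the indoor:outdoor ratio differs between arms. A cluster intercept raises or lowers both positions together, so it drops out of that ratio. If some houses or villages have a persistently higher indoor share than others, the stated model has nowhere to put this variation except the within-cluster residual. It then averages that residual over every catch as if each were new information about the ratio.

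The protocol uses landing catches to learn how the repellent changes host-seeking behaviour, and this term shows whether the effect differs indoors and outdoors. At stake is the credibility of its interval: ordinary differences between houses or villages could look like a location-specific repellent effect.

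**Working it through.** **Counts, from the protocol**
- Houses: 12 clusters × 4 = 48, which reproduces the stated 48.
- Rounds: 24 months, quarterly = 8.
- Catches: 48 × 8 rounds × 2 nights × 2 positions = 1,536. Per cluster and position: 4 × 8 × 2 = 64.
- If each house is caught on one night per round: 48 × 8 × 1 × 2 = 768, or 32 per cluster and position.

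The protocol gives no variance component, alpha or error rate for this model, so there is no such figure to reproduce. Every variance below is an assumption.

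**Variance ratio on the log scale**

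Let C² be the cluster-by-location variance, L² the house-by-location variance (each per position), H² the variance of a house effect shared by both positions, R² the residual variance, and n the catches per cluster and position.
- True variance of a cluster's mean at one position, leaving out effects that cancel in the contrast: C² + L²/4 + R²/n.
- Variance the stated model uses: (R² + H² + L² + C²/2)/n.
- SE ratio = square root of (true/model). Error at nominal 5% = 2 × [1 − Φ(1.96/ratio)].

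With R² = 1, H² = 0.25 and n = 64:

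| C² | L² | True | Model | SE ratio | Error |
|---|---|---|---|---|---|
| 0 | 0 | 0.0156 | 0.0195 | 0.89 | 2.8% |
| 0 | 0.05 | 0.0281 | 0.0203 | 1.18 | 9.6% |
| 0 | 0.10 | 0.0406 | 0.0211 | 1.39 | 16% |
| 0.02 | 0 | 0.0356 | 0.0197 | 1.35 | 15% |
| 0.05 | 0.10 | 0.0906 | 0.0215 | 2.05 | 34% |

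With n = 32 the third row becomes 0.0563 against 0.0422: ratio 1.15, error 9%.

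The first row shows that a shared house effect alone makes the test slightly conservative. The inflation comes only from C² and L².

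**Simulation with no true interaction, two-sided 5% Wald test, 1,536 negative binomial catches**

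The stated model was fitted with cluster intercepts as fixed effects, which should give practically the same interaction test as a random cluster intercept.
- Set A: mean 5 with seasonal variation, dispersion 0.7, cluster SD 0.5; house SD 0.5 in the rows with location-specific variation; 600 runs.
- Set B: mean 5, dispersion 1.5, cluster SD 0.5, house SD 0.3, cluster-by-quarter SD 0.5, house-night SD 0.3; 400 runs.

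| Location-specific SD (log scale) | Set A | Set B |
|---|---|---|
| None | 4.2–5.2% (house SD 0 to 0.6) | 3% |
| House-by-location 0.15 | – | 7% |
| House-by-location 0.2 | 14% | – |
| House-by-location 0.25 | – | 8% |
| House-by-location 0.3 | 20% | – |
| House-by-location 0.4 | – | 20% |
| House-by-location 0.5 | 35% | – |
| Cluster-by-location 0.1 | 10% | – |
| Cluster-by-location 0.2 | 28% | 18% |
| Cluster-by-location 0.3 | 40% | – |
| Both 0.2 | – | 23% |
| Both 0.3 | 42% | – |

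With 768 catches, set B gives 5%, 7% and 9.5% at house-by-location 0.15, 0.25 and 0.4, and 12% at cluster-by-location 0.2. Other runs agree on direction but not on size. A mixed-model fit under the set B assumptions gave 30% at house-by-location 0.4. A further run gave 7–18% over 0.2–0.4 and 15% at cluster-by-location 0.2.

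**Which analysis repairs it** (set A, house SD 0.5, 400 runs)

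| Location-specific SD | As stated | Plus house intercept | t-test on 12 cluster log ratios, 10 df |
|---|---|---|---|
| None | 4.8% | 7.0% | 7.0% |
| House-by-location 0.3 | 20% | 18% | 5.8% |
| Cluster-by-location 0.2 | 28% | 34% | 4.8% |
| 0.3 and 0.2 together | 33% | 34% | 4.8% |

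A house intercept does not cure the problem; the cluster-level contrast stays near nominal.

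**Average SR effect.** This is a between-cluster comparison that the cluster effect largely covers. A z-based Wald test with only 10 df has about 7.8% error (two-sided tail of t with 10 df beyond 1.96), whatever the house variance.

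**The case against.** Several points on the other side stand.

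- **Repeated sampling is not itself the fault.** A reader might infer that returning to the same houses inflates the test, or that the catches are treated as fully independent. Neither is right. The model conditions on cluster, and a house effect shared by both positions cancels. For the same reason the comparison with the child-level random effect goes only so far: its direct analogue is a house intercept, which is not enough here.
- **The size is not in the documents.** A reader might infer an error rate several times nominal as a fact of the design. That needs location-specific variation which the protocol does not quantify. Sentinel houses are also to be balanced on design and inhabitants, which may reduce the variation without removing it.
- **No test is announced.** The formal hypotheses concern malaria only, and no alpha or decision rule is attached to the interaction. Nor does the term visibly set the entomological benchmarks: the analysis linking entomology to malaria uses HBR averaged over a cluster's sentinel houses, not this coefficient.
- **The catch count is uncertain.** There are 16 collectors, a new team takes over at midnight, and one pair of clusters (8 houses) is worked per night. If the 16 cover both shifts, 8 per shift staff 4 houses, which gives 768 catches and less inflation. *Trial design {8}* also calls the landing catches indoor, but the outcome list, the collection procedure and the model all have both positions.
- **Detail may sit in the SAP.** The count distribution is left open until the data are seen. The random part, however, is stated, and as stated it does not match the interaction placed beside it. This is therefore a point about a stated model, not about missing detail.

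**Conclusion.** The point holds conditionally. As written, the HBR model understates the standard error of the location-by-intervention term whenever the indoor:outdoor ratio varies between houses or clusters. Over assumed log-scale SDs of 0.1 to 0.5, simulated error at nominal 5% runs from near nominal to about 40%, and it is lower with 768 catches. With no such variation the term is sound.

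The documents do not support reading this as a flaw in the average SR/placebo ratio or in any malaria analysis. They also do not support any single inflation factor. The mechanism is certain; the size is not. The consequence is an over-narrow interval for one term on a secondary endpoint. The parity and sporozoite models reuse the same covariates, but no calculation was made for them.

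**What to change.** In *Effects of SR on entomological endpoints*, for the landing-catch models, keep the cluster effect and add random effects for house within cluster, cluster-by-location and house-by-location. State that if this model does not converge, the interaction will be estimated from each cluster's log indoor/outdoor ratio, comparing 6 with 6 clusters by a t-test on 10 df.

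The cost is a change of wording and a few more variance terms, with no new data. The interval for the interaction becomes wider, and with only 12 clusters the fallback may be needed.

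### Parity is a yes/no result in a capped, dissected sub-sample, but the plan models it as a Poisson or negative-binomial count with the whole catch as offset

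*Protocol article*

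**What the plan says.** The section on effects of SR on entomological endpoints leaves the distribution for HBR to be chosen once the data have been examined. For parity it commits: "The model for parity rate will be the (zero-inflated) Poisson distribution or a (zero-inflated) negative binomial distribution". The sentence goes on to name what is counted and what it is divided by: "with the daily porous mosquitos as the outcome and the daily HBR as the offset". The covariates are those of the HBR model, including "a random effect for cluster". The same section defines the offset variable as "HBR (number of anopheline caught during the 12-hr interval overnight", that is, the whole catch.

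Parity is measured on something smaller. Outcomes {12}, item 6, defines it "as measured by mosquito ovarian dissections from a sub-sample of anophelines collected during HLC procedures". Entomological collections sets the limit: "A subset of up to 30 per cluster per sampling period will be dissected for parity". The sampling frame is also small: "HLCs will be done indoors and outdoors in 6 intervention and 6 control clusters", and each round of collection takes place only "once every quarter (3 months".

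No binomial option is named for parity, and the number dissected appears nowhere in the model.

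**The concern.** Given n dissected females with parity p, the parous count is bounded by n and has variance np(1-p). A Poisson model assigns np. A negative binomial, or zero inflation of either family, adds variance to that. No listed option can therefore reach the binomial variance, and none stops a fitted rate from exceeding 1.

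The offset is a second fault in the same sentence. The numerator is limited by the number dissected, but the offset is the number caught. Once a catch passes the cap, the offset keeps growing while the parous count cannot.

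Parity is a secondary outcome and is named among the entomological correlates in the secondary objectives. At stake is whether the trial can estimate a change in mosquito age structure without either masking it or giving it the wrong sign.

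**Working it through.** The article gives no parity level, expected fall, dissection yield or power for parity, so there is no figure of the plan's own to reproduce.

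**Inputs from the article.** 6 clusters per arm; quarterly rounds over 24 months = 8 rounds; cap 30. Ceiling: 30 × 6 × 8 = 1440 dissected per arm.

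**Assumed, with ranges.** Parity 0.3 to 0.8; relative fall 5% to 20%; 360 to 1440 dissected per arm; two-sided 5% test (no alpha is stated for parity); between-cluster SD from zero upward.

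**Case 1: the denominator matches the number dissected** (the cap rarely binds, or only the offset is corrected). For the log parity ratio:
- true variance = sum over arms of (1-p)/(np)
- Poisson variance = sum over arms of 1/(np)
- Poisson power = Φ((|log ratio| − 1.96·SE_Poisson)/SE_binomial)

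Example, 0.70 to 0.63 with n = 720 per arm:
- binomial variance = 0.30/504 + 0.37/453.6 = 0.00141, SE 0.0376
- Poisson variance = 1/504 + 1/453.6 = 0.00419, SE 0.0647
- |log 0.9| = 0.1054
- binomial power = Φ(0.1054/0.0376 − 1.96) = 80%
- Poisson power = Φ((0.1054 − 1.96 × 0.0647)/0.0376) = 28%

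Other settings without cluster variance:

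| Parity | Dissected per arm | Binomial | Poisson |
|---|---|---|---|
| 0.70 to 0.63 | 1440 | 98% | 72% |
| 0.70 to 0.63 | 360 | 51% | 8% |
| 0.50 to 0.45 | 1440 | 76% | 49% |
| 0.50 to 0.45 | 720 | 47% | 21% |
| 0.30 to 0.27 | 1440 | 43% | 30% |

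With falls of 15% or more, parity of at least 0.5 and 1440 dissected per arm, Poisson keeps at least 93% of the binomial power. The nominal 5% test has a true size of about 1.9%, 0.6% and 0.03% at parity 0.3, 0.5 and 0.7.

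Cluster variance dilutes the loss. Adding 2τ²/6 with τ = 0.10 on the log-parity scale (1440 per arm, 0.70 to 0.63) gives 38% against 27%. Across τ of 0.10 to 0.15 and falls of 10% to 20%, Poisson keeps 70% to 95% of the binomial power. With a small cluster SD the loss can still exceed half. At 720 per arm and logit SD 0.1, the added variance is (0.030² + 0.037²)/6 = 0.00038, so the true SE is 0.0423. If the Poisson random effect shrinks to zero, power is 70% against 31%.

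**Case 2: the HBR offset as written, with the cap binding.** If every round hit the cap, the modelled rate would be 30p/HBR, so a 30% fall in HBR with unchanged parity would give an apparent parity ratio of 1/0.7 = 1.43. A simulation assumed a mean catch of 60 per cluster-round, negative-binomial catches with k = 2, parity 0.7, no cluster effect and model-based Poisson errors:
- no effect on HBR or parity: about 49% false rejections, 24% in each direction
- HBR down 30%, parity unchanged: estimated ratio 1.31, with a significant false increase in 91% of runs
- HBR down 30%, parity truly down 10%: estimated ratio 1.17, the wrong direction

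With a mean catch of 10 the cap rarely binds and case 1 returns: for a 10% fall from 0.7, power is 65% binomial against 18% Poisson with the HBR offset.

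**The case against.** The strongest objection is that overstated variance and halved power describe only one regime. With the offset as written and the cap binding, the Poisson test rejects too often. If each of the 4 houses is worked indoors and outdoors on both nights there are 16 collector-nights per cluster-round, or 8 on a narrower reading. The cap then binds at 30/16 ≈ 1.9 to 30/8 ≈ 3.8 anophelines per collector-night. The article does not say which regime to expect. This stands, and it is why the fault has to be stated for both regimes.

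It is also fair that 1/(1-p) is a within-cluster ratio, while the plan has a cluster random effect. In a simulation with the dissected offset, up to 30 dissected per round and parity 0.7, the ratio of printed standard error to true SD was 1.43, 1.08 and 0.91 for logit SD 0.1, 0.2 and 0.3. The overstatement fades and then reverses. The calculations are also simpler than the planned daily model with time and location terms, and a negative binomial might absorb the excess variation in case 2, though not the bias.

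The absence of the SAP is not an answer, because the model family and offset are stated here without a hedge.

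A reader might also infer that benchmark thresholds for future products would be misstated. The article does not support that. The analysis relating entomological to malaria endpoints enters the parity rate as a covariate in cloglog models and does not use this model's standard errors.

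**Conclusion.** The stated parity model is wrong whichever regime applies. Where the denominator effectively equals the number dissected, within-cluster variance is overstated by about 1/(1-p), and none of the listed families can correct it. Where catches exceed the cap, the parity ratio is biased upward if the repellent lowers HBR, and Poisson intervals are too narrow.

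The algebra and the mismatch between offset and dissection cap follow from the article. The sizes do not: they rest on assumed parity, effect, dissection yield, catch size and cluster SD. The power loss in the first regime runs from little (large falls at the ceiling, or larger cluster SD) to more than half (small falls, fewer dissections, low cluster SD). It would be wrong to read this as a general halving of power. The primary malaria analysis is not affected.

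**What to change.** In the section on effects of SR on entomological endpoints, model the number parous out of the number dissected with a binomial mixed model (logit link, cluster random effect), moving to a beta-binomial if there is overdispersion. Remove the Poisson, negative-binomial and zero-inflated options and the HBR offset for parity. Report parity by arm with an odds ratio or a difference and its interval. Correcting only the offset would leave the variance fault in place.

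For sporozoites, positives out of the number tested may take the same form. With rare positives Poisson is close to binomial, so the variance gain there is small.

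The cost is a change of wording in the article's analysis section and the SAP. The numbers dissected and parous come from the dissections already planned.
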